### Recruitment

2.6

Recruitment of the participants began in September 2017 and is expected to finish in January 2020. Before inviting participants to sign the informed consent, information on the study goals and procedures will be provided verbally. The participants will be also invited to raise questions or doubts on any aspect of the study. Data confidentiality guarantees will be provided to participants by the principal investigator. Written consent will be obtained from all participants before registration, and participants may withdraw from the trial at any point in time without penalties. The written consent form includes information regarding the background and purpose of the study, therapeutic interventions, outcomes, and the expected benefits and drawbacks.

### Randomization and blinding

2.7

Participants will be allocated to the 2 groups in a random manner through a sequence of numbers that will be generated by a computer program before beginning the selection process. The group assigned to each patient will be kept in a sealed envelope with the objective of concealing the assignment to the researcher, who will decide on the entry of subjects to the study (Fig. 2). Given the nature of the therapeutic interventions studied, physiotherapists and patients, blinding will be not possible. The evaluator and statistician, however, will not know to which group the subjects evaluated will belong.

**Figure 2 F2:**
[figure not shown]
Flow diagram of patients through phases of clinical study.

### Data management

2.8

Information obtained from the evaluation of each participant will be recorded on a paper print-out. The information will then be hand written on a paper document case report form and entered into an Excel file for future statistical analyses. In accordance with the Personal Information Protection Act, the names of all participants will not be disclosed and a unique identifier number given during the trial will be used to identify participants. All of the participants will be informed that the clinical data obtained in the trial will be stored in a computer and will be handled with confidentiality. The participants’ written consent will be stored by the principal investigator.

### Statistical analysis

2.9

The continuous variables will be presented as means and standard deviations, and the categorical ones as number and percentage; to determine whether parametric statistical tests are appropriate for use in the analysis of the data, the fitting to normal distribution will be evaluated using both statistical (Shapiro-Wilk test) and graphical (normal probability plot) methods. To examine baseline differences of 2 groups, a 1-way analysis of variance (for continuous variables) and chi-square tests (for categorical variables) will be conducted. Repeated measures analysis of covariance will be performed on outcome variables with time (3 levels: preintervention, postintervention, and 1-year postintervention) as the within-subject factor and with type of intervention (2 levels: specific exercise program vs home exercises). The covariates were baseline values of each outcome variable.

Data will be processed independently by 2 researchers, and inconsistencies will be detected using the VALIDATE command of Epi Info (CDC) software. After checking the truthfulness of outliers and extreme values, these will be winsorized using below the 1st percentile and above the 99th percentile of the distribution of variables. Before conducting the study, after considering the nature of the missing data in those patients with incomplete entries, these will be imputed using chained equations.

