### Sample size calculation

2.5

Sample size for this trial is based on an expected mean difference between groups of 17 points of the Constant-Murley questionnaire, which is the minimum clinically important difference.^[53]^ The mean assumed for the calculation was 52.5 with a standard deviation of 23 points based on results of other randomized clinical trials.^[40]^ To detect this difference between both treatments, with a value of α = 0.05 (probability of committing a type I error) and a statistical power of 90%, a minimum of 39 patients per group is needed. This minimal sample size estimate has been increased by 20% after considering the potential dropouts, totaling 47 patients for each group. According to this, the experimental hypothesis proposed is that there will be a difference of at least 17 points in the Constant-Murley questionnaire in the intervention versus control group that will follow a program of exercises at home. Sample size was performed using the Stata SE software, version 15 (StataCorp, College Station, TX).

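### The baseline score is both an outcome level and the covariate in the repeated measures ANCOVA, so a reported group main effect would be exactly two thirds of the mean follow-up effect

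*Protocol article*

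**What the plan says.** The Statistical analysis section (2.9) of the protocol article fixes the model in two sentences. The first names the method: "Repeated measures analysis of covariance will be performed on outcome variables". The model has two factors. Treatment arm is the between-subject one; the other is given as "time (3 levels: preintervention, postintervention, and 1-year postintervention) as the within-subject factor", so the preintervention score is itself an outcome level. The next sentence adds: "The covariates were baseline values of each outcome variable". This applies to every outcome, including the primary one, the Constant-Murley score. The section does not say whether the group main effect, the group-by-time interaction or a contrast at one visit is the answer to the trial's question.

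The Sample size calculation section (2.5) sets the yardstick. It uses an "expected mean difference between groups of 17 points of the Constant-Murley questionnaire, which is the minimum clinically important difference", and it words the experimental hypothesis as a difference of at least that size between the groups.

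**The concern.** A baseline measurement can enter a longitudinal model as part of the outcome vector or as a covariate. Here it does both. Once the preintervention score is adjusted for itself, nothing is left to explain at that time level: the adjusted group difference is zero by construction, whatever the treatment does. A group effect averaged over all three levels then includes that forced zero.

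What is at stake is the size of the reported effect. The protocol invites the reader to hold the group difference against 17 points. An estimate on a scale compressed by one third, set against that figure, could make a treatment that meets the protocol's criterion look as if it had missed it. The confidence interval is compressed by the same factor, so it gives no warning.

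**Working it through.** **Inputs.** From the Sample size calculation section: difference 17 points; "The mean assumed for the calculation was 52.5 with a standard deviation of 23 points"; "with a value of α = 0.05 (probability of committing a type I error) and a statistical power of 90"%; and the statement that "a minimum of 39 patients per group is needed". From the Statistical analysis section: three time levels, two groups, baseline as covariate. The protocol gives no correlation between visits, so 0.3 to 0.7 is assumed wherever one is needed.

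**1. The plan's own figure.** n per group = 2 × (1.960 + 1.282)² × 23² / 17² = 38.5, rounded up to 39. With the 20% increase, 39 × 1.20 = 46.8, that is 47. The sample size reproduces (two-sided) and does not depend on the point at issue.

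**2. The group main effect.** In a repeated measures ANCOVA with complete data, the between-subject part is a regression of each patient's mean over the time levels on group and baseline. Let d12wk and d1yr be the adjusted group differences at follow-up. Regressing the baseline score on group and on itself gives a group coefficient of exactly 0. Hence

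- three levels: main effect = (0 + d12wk + d1yr) / 3
- two follow-up levels: main effect = (d12wk + d1yr) / 2
- ratio = (1/3) / (1/2) = 2/3, whatever the correlations.

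With 17 points at both visits: (0 + 17 + 17) / 3 = 11.33. In simulation (39 per group, SD 23, 4,000 trials per scenario, four correlation patterns) the three-level estimate averaged 11.32 to 11.39 and the two-level estimate 16.97 to 17.08, with a ratio of 0.6667.

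**3. The test of that effect.** The residual at the baseline level is also exactly 0, so the residual of the three-level mean is two thirds of the residual of the two-level mean, and the standard error shrinks by the same 2/3. The simulated t statistics agreed to about 1e-13. Type I error was 0.046 to 0.053 and power 0.97 to 1.00 in both models.

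An illustration at equal correlations of 0.5, ignoring chance imbalance at baseline:

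- residual variance of the two-visit mean = 529 × [(1 + 0.5)/2 − 0.5²] = 264.5
- standard error = √(264.5 × 2/39) = 3.68; two thirds of this is 2.46
- two levels: 17 ± 1.96 × 3.68, or 9.8 to 24.2
- three levels: 11.33 ± 1.96 × 2.46, or 6.5 to 16.1

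Both give t = 4.6, but the second interval lies wholly below 17 although the true difference is 17. The same formula gives upper limits of 16.4 at correlation 0.3 and 15.4 at 0.7.

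**4. Group-by-time.** This term is not diluted. The zero-variance level disturbs sphericity only modestly (epsilon 0.90 to 0.96). Simulated type I error was 0.048 to 0.056 uncorrected and 0.045 to 0.051 with the Greenhouse-Geisser correction.

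**5. A fit with one variance pooled over the three levels.** This is a conditional check, because the plan names no such model. With a baseline-by-time slope, the pooled residual variance is (0 + σ² + σ²)/3 = (2/3)σ². The standard error at 12 weeks is then √(2/3) = 0.82 of what it should be, and the false-positive rate is 2 × [1 − Φ(1.96 × 0.816)] = 11%. Random-intercept simulations at correlation 0.5 gave a model standard error of 3.69 against an empirical 4.51 (ratio 0.82) with that slope, and 3.89 against 4.70 (ratio 0.83) with a common slope. A smaller run gave 3.87 against 4.55 (ratio 0.85). Across six scenarios with correlations of 0.3, 0.5 and 0.7, rejection under no effect was 9.3% to 11.1%.

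**The case against.** The strongest defence is that the protocol names a repeated measures ANCOVA, and in that method the test of the group effect is intact. This stands. A reader might infer that the error term is wrong or that the trial loses power. Putting 11.33 points and an unchanged SD of 23 into the sample size formula would suggest about 59% power at 39 per group, or 87 per group for 90%. Neither inference is supported, because estimate and standard error shrink together (step 3). Likewise, a false-positive rate of about 10% cannot be charged to the plan as written, because it belongs to a pooled-variance fit that the protocol does not mention.

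The second defence is that only one coefficient is affected. The introduction asks about effectiveness in the short and long term, and measurements are at 12 weeks and 1 year, which points towards visit-specific comparisons. This also stands, and it makes the harm conditional: nothing in the text says that the three-level average will be compared with 17 points. But nothing excludes it, since the term that answers the hypothesis is not named.

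A third caution concerns an effect present only at 12 weeks. The three-level main effect would be 17/3 = 5.7 points, but the two-level one would already be 17/2 = 8.5. Only the step from 8.5 to 5.7 comes from using baseline twice; the rest is ordinary averaging over visits.

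The defence does not remove the double use itself. It is stated outright, and it is not a detail that an article leaves to a fuller document.

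**Conclusion.** The model is wrongly specified as written: baseline should not be both a level of the outcome and the covariate. If the group main effect is the reported result, it is exactly two thirds of the mean follow-up effect, and a true 17 points at both visits appears as about 11.3. The factor is exact for complete (or imputed) data and needs no assumption about correlations.

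The finding concerns the size of the reported effect against the protocol's own threshold. It does not concern the validity or power of the group test or the sample size, and it does not reach group-by-time or visit-specific contrasts in the named ANCOVA. The one route to a wrong standard error is a visit contrast from a fit with variance pooled over all three levels: the 12-week standard error would be about 15 to 20% too small, with about 10 to 11% false positives, at assumed correlations of 0.3 to 0.7.

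**What to change.** Use baseline once, and name the contrast that answers the hypothesis. Either of these will do:

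- Make time a two-level factor (12 weeks and 1 year), keep the baseline value of the outcome as covariate, and report the adjusted group difference with its 95% confidence interval at each visit, to be read against 17 points.
- Keep three time levels, drop the baseline covariate, and base the conclusion on the group-by-time contrasts, or constrain the baseline means of the two groups to be equal.

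The choice of covariance structure can be left to the analysis plan, provided that the baseline level does not feed a pooled residual variance while it is also the covariate. The cost is one sentence in the analysis section, with no new data, no further patients and no change to the sample size. It should be settled before the data are analysed.

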### Harms

2.10

To collect, assess, report, and manage the potential adverse effects of the interventions that will be performed in the study, at the beginning and end of each treatment session, patients from both groups will have a logbook available. According to the informed consent that patients will sign when they are recruited for the study, patients who show an increase in symptoms after 48 hours of the session will require an immediate evaluation by an orthopedic surgeon.

### Ethics

2.11

The study will be conducted under the Declaration of Helsinki principles,^[54]^ and the norms of good clinical practice. The study protocol has been approved by the Ethical Committee of the Central Metropolitan Health Service of Chile with the reference number 048975. This research was registered in the Brazilian Registry of Clinical Trials with the number U1111-1210-3555.

## Discussion

3

The aim of this article was to describe the rationale and methods of a randomized controlled trial aimed to test the effectiveness of 2 exercise programs in patients with stage 2 SIS, with poor response to initial conservative treatment, who were under evaluation for surgery. The intervention group will receive a program of specific exercises, taking as reference the clinical decision algorithm proposed by a panel of experts.^[27]^ For its part, the control group will receive a program of nonspecific exercises to perform at home.

There are several modalities of exercise used in the management of SIS.^[20–22,26]^ Therapeutic exercise has been shown to reduce pain and improve functional loss associated with SIS;^[20–26]^ however, specific components of the exercise protocol are unknown.^[20–22,24,26]^ A systematic review showed that programs including a combination of scapular stabilization exercises, rotator cuff resistance exercises, active exercises to improve range of motion, and muscle stretching exercises were effective in the management of SIS.^[24]^ Nevertheless, the evidence is limited, making it difficult to establish which type of exercise is more clinically effective.^[24–26]^

Based on the alterations of glenohumeral and scapular kinematics associated with the SIS, the expert consensus has recommended including specific exercises to treat muscle function deficits, which can be subdivided in neuromuscular control deficits (muscle cocontraction and force couples) and muscle strength deficit, which also includes an imbalance in muscle activity and an alteration of muscle activation times.^[22,31,55]^ Another recently published systematic review, however, concluded that there is insufficient evidence to support or refute the effectiveness of specific exercises used in the conservative treatment of patients with SIS.^[56]^

The general principles of our exercise protocol are exercises should be performed with optimal scapular positioning and control without abnormal compensatory trunk movement; start with low load/low activation exercises, without pain, with the arms below the shoulders level, emphasizing the quality of the performance of the motor task, performed slowly, consciously, and progressively; progress to prone and lateral decubitus exercises that increase the load, selectively activating weak muscles such as serratus anterior and inferior trapezius, with minimal activation of overactive muscles such as upper trapezius and deltoids, avoiding muscle fatigue; and decrease in feedback gradually during the course of the exercise, until the realization of exercises subconsciously and automatically.^[27,31,55]^

To strengthen the reliability of the results, important methodological factors have been considered planning this study. To avoid selection bias, a clinical and imaging diagnosis of the SIS was considered, including echotomography and magnetic resonance imaging; participants will be randomly assigned to the groups through a hidden allocation sequence. Furthermore, adjusting the sample size for possible losses or dropouts and increasing the number of patients recruited by 20% was considered; in the event of loss or withdrawals, statistical analysis will be carried out by protocol and intention to treat. To minimize measurement bias, all evaluations will be performed by 2 physiotherapists external to the research team, who will also remain blinded in relation to the treatment groups; the statistician will remain blinded to the group assignment of the participants; The outcome measures used are suitable and frequently used in clinical practice, as well as having good levels of validity and reliability. The 1-year follow-up will allow the effectiveness of the therapeutic interventions to be established in the long term.

Our study has some limitations. One important limitation is that the clinical decision algorithm proposed by a panel of experts has not yet been validated. Finally, the blinding of physiotherapists and patients was not achievable given the nature of the interventions studied.

To the best of our knowledge, this is the first clinical trial that compares a specific exercise program based on a clinical decision algorithm proposed by a panel of experts, with a program of nonspecific exercises performed at home. The results of this study will add evidence to the limited and controversial body of knowledge related to the effectiveness of the different modalities of therapeutic exercises that are prescribed for patients with SIS.
